**Key Outcomes**:

- Surgical duration (minutes).
- Implant placement accuracy (via postoperative CBCT).
- Postoperative complications (within 30 days).
- Early implant failure rates (within 6 months).
- Patient satisfaction (via validated 10-point questionnaire at 6 months).
- Implant stability (via Resonance Frequency Analysis at 3, 6, and 12 months).
- Pain and swelling (via Visual Analogue Scale on Days 1 and 3).

**Study Duration**: January 6, 2025 (recruitment start) to August 3, 2025 (final follow-up).
**Sample Size**: 90 patients (30 per group), calculated for 80% power and alpha of 0.05, assuming a medium effect size (Cohen’s d = 0.5) for implant placement accuracy, with a 10% dropout rate.

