**6. Methodology**

**Randomization**: Computer-generated randomization (1:1:1 ratio), stratified by age and gender, will assign participants to FHIS, PDIS, or FGIS groups.

**Blinding**: Surgeons and participants cannot be blinded due to the nature of the interventions. Outcome assessors (radiologists, statisticians) will be blinded to group allocation to reduce bias.

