**Interventions**:

- **FHIS**: Implants placed using clinical judgment, with minimal surgical guides.
- **PDIS**: Pilot drill used for initial osteotomy, followed by sequential drilling.
- **FGIS**: Customized surgical guides based on CBCT and planning software ensure precise implant placement.

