**Statistical Analysis**:

- Descriptive statistics: Mean, SD for continuous variables; frequencies for categorical variables.
- Normality testing: Shapiro-Wilk test.
- Comparative analysis: One-way ANOVA with Tukey post hoc test for group differences.
- Subgroup analysis: Canine vs. molar implants.
- Software: SPSS (Version 23).
- Significance level: $p < 0.05$.
- Analysis will follow an intention-to-treat approach.

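### Randomisation is stratified by age and gender, but the one-way ANOVA fixed for group comparisons omits both factors and so gives up precision

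*Protocol*

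**What the plan says.** Section 6 of the protocol, under Randomization, specifies "Computer-generated randomization (1:1:1 ratio), stratified by age and gender". Under Statistical Analysis in the same section, the comparison method is "Comparative analysis: One-way ANOVA with Tukey post hoc test for group differences". No covariate, stratification term or second between-group method is named there.

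Two neighbouring lines bear on how far the point reaches. The descriptive line reads "Mean, SD for continuous variables; frequencies for categorical variables", and the only assumption check is "Normality testing: Shapiro-Wilk test". Section 3 lists complications and early implant failure among the key outcomes, alongside the continuous ones. It sets the sample size at 30 per arm, for d = 0.5 on placement accuracy, with 10% dropout. The protocol gives no standard deviations by arm, no event rates and no explicit plan for confidence intervals.

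**The concern.** Stratified randomisation is used because the factors are thought to matter for outcome. When it works, the arms are balanced on age and gender, and the part of the outcome that these factors explain cancels from the difference between arms. The one-way ANOVA does not use this: its within-group mean square still carries the variation due to age and gender, so the standard error of each contrast is larger than it should be. The test then rejects too rarely under the null and has less power than the design has paid for. With 27 analysed patients per arm, precision is scarce, and this part of it can be recovered without recruiting anyone.

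**Working it through.** **Inputs from the protocol.** 30 per arm, 10% dropout, hence 30 × 0.9 = 27 analysed per arm; d = 0.5; alpha 0.05, taken as two-sided because the protocol does not say. **Assumption.** R², the share of outcome variance explained by age and gender, is not given; 5, 10 and 20% are used. The error calculation also assumes that randomisation achieves balance within strata.

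**The plan's own figure.** The stated 90 patients for 80% power at d = 0.5 does not reproduce. A two-sided two-group comparison needs 63 per arm, 70 after dropout, 210 in all. That is a separate matter and nothing below rests on it, but it explains why the starting power is 44% and not 80%.

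**Error of the unadjusted comparison.** Under balance, the difference between two arms has variance 2σ²(1 − R²)/n, but the unadjusted analysis estimates it as 2σ²/n. The test statistic therefore has standard deviation √(1 − R²), and

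true error = 2 × [1 − Φ(1.96/√(1 − R²))].

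**Power of the adjusted comparison.** The effect in residual SD units is 0.5/√(1 − R²). The noncentrality is that value times √(27/2) = 3.674, and power is read from the noncentral t with 52 df.

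| R² | 1.96/√(1 − R²) | True error, unadjusted | Adjusted d | Noncentrality | Power |
|---|---|---|---|---|---|
| 0 | 1.960 | 5.0% | 0.500 | 1.837 | 44% |
| 0.05 | 2.011 | 4.4% | 0.513 | 1.885 | 46% |
| 0.10 | 2.066 | 3.9% | 0.527 | 1.936 | 48% |
| 0.20 | 2.191 | 2.8% | 0.559 | 2.054 | 52% |

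The gain is equivalent to a larger sample of 27/(1 − R²) per arm: 28.4, 30.0 and 33.8.

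At the stricter Tukey threshold (critical t 2.389 on 78 df), the same noncentralities give 30% unadjusted and 31, 33 and 37% adjusted.

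**Check by simulation.** This used 40,000 null trials per setting, four balanced strata and 28 per arm. The unadjusted overall F-test rejects in 5.0, 3.4, 2.6 and 1.3% of trials when the strata explain 0, 10, 20 and 30% of variance. With strata in the model, it rejects in 4.9 to 5.2%.

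**Conditional refinement on spread.** Tukey pools one SD over the arms. If the SDs for freehand, pilot-drilled and fully guided were 2 : 1.5 : 1 (an assumption), simulated per-pair Tukey error with 27 per arm is about 3.8% for freehand against pilot-drilled, about 2.1% for freehand against fully guided and 0.5% for pilot-drilled against fully guided. The equal-SD value is 1.9%. Familywise error is only about 5.4 to 5.6%. Power for a pilot-drilled versus fully guided difference of 0.8 fully guided SDs would be 28% with Tukey and 46% with Games-Howell.

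**The case against.** The best defence is that an unadjusted test after stratified randomisation remains valid, that the loss is small if the factors are weak (44% to 46% at R² = 5%), and that covariates are often settled in a statistical analysis plan, which is not at hand. The first two stand and limit the point to efficiency. The third stands only in part: the protocol does not leave the model open but fixes one that, by name, has no covariates, so a later adjusted analysis would depart from it.

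Three stronger readings are tempting and are not supported.

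- **Wrong p-values and intervals.** Omitting the strata makes the test conservative. No intervals are explicitly planned, so none can be wrong.
- **Arms known to differ in spread.** The Interventions text says "Customized surgical guides based on CBCT and planning software ensure precise implant placement". A reader might infer smaller variance in the guided arm, but no SD by arm is given and the sentence bears on placement accuracy alone. Even under the assumed 2 : 1.5 : 1, the freehand versus fully guided comparison stays near nominal and the familywise error hardly moves.
- **ANOVA applied to complications and failures.** The plan gives categorical variables frequencies and never says that they enter the ANOVA. If they did, 0/30, 0/30 and 3/30 events would give an overall p of 0.045 against an exact 3 × C(30,3)/C(90,3) = 3 × 4,060/117,480 = 0.104. But the smallest Tukey p is 0.077, so no pairwise difference would be declared. Tukey's simulated familywise error is 0.2 to 0.3% at a 2% event rate and 1.8 to 2.1% at 5%, which is conservative. An unnamed categorical test is largely a matter for the statistical analysis plan.

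**Conclusion.** The stated analysis does not follow the stated randomisation: it leaves out the two factors used to stratify. The consequence is a conservative test and lost precision. The size, error of about 4.4 to 2.8% in place of 5% and a forgone gain of 2 to 8 percentage points in pairwise power, rests on the assumed R² of 5 to 20%. At R² = 0 nothing is lost except the degrees of freedom. If randomisation did not achieve balance within strata, the unadjusted error would sit closer to 5%, but adjustment would still improve precision. Unequal spread is a conditional refinement for placement accuracy. The method for complications and failure needs clarifying and is not an error in the plan. The change is worth making because it is nearly free, and it should be made before the data are seen.

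**What to change.** In Statistical Analysis, replace the one-way ANOVA for continuous outcomes with a linear model (ANCOVA) containing treatment, age and gender; continuous age is acceptable. Report adjusted pairwise differences with multiplicity-controlled 95% intervals. With 81 analysed patients, residual degrees of freedom fall from 81 − 3 = 78 to 76 or 75.

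Optionally, specify robust or group-specific variances for placement accuracy, to cover the possibility that spread differs by arm.

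Add one sentence saying that this model applies to continuous outcomes only, and that any comparison of 30-day complications and 6-month implant failure uses an exact test.

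The cost is a short amendment and a little more analysis work. No patient procedure, visit or sample size changes.

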**4. Participant Recruitment**

**Inclusion Criteria**:

- Adults aged ≥18 years.
- Partial edentulism (missing one or more teeth in an arch with remaining natural teeth).
- Sufficient bone volume and quality for implant placement (confirmed by CBCT).
- No systemic contraindications for surgery.

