**4. Imaging Parameters**

To ensure reproducibility and diagnostic accuracy, the following standardized parameters will be used:

- **Field of View (FOV)**:
  - Small FOV (5x5 cm or 8x8 cm) for single-tooth or small-segment edentulous areas.
  - Medium FOV (10x10 cm) for larger edentulous spans or multiple implants, ensuring inclusion of adjacent teeth and anatomical landmarks (e.g., inferior alveolar nerve, maxillary sinus).
- **Voxel Size**: 0.2 mm for high-resolution imaging to assess fine bone details and implant positioning.
- **kVp**: 90 kVp (range: 80–100 kVp, adjusted based on patient size to optimize image quality).
- **mA**: 5–10 mA, adjusted to minimize radiation dose while ensuring diagnostic clarity.
- **Exposure Time**: 10–15 seconds, depending on the FOV and patient cooperation.
- **Rotation**: 360° for comprehensive 3D reconstruction.
- **Image Format**: DICOM (Digital Imaging and Communications in Medicine) for compatibility with implant planning software.

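### Several implants per patient are allowed, but the only comparison named, one-way ANOVA, is valid only with one value per patient, and the unit of analysis is not stated

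*Protocol*

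**What the plan says.** **Unit of randomisation and sample size.** Protocol section 6 (Methodology): "Computer-generated randomization (1:1:1 ratio), stratified by age and gender, will assign participants to FHIS, PDIS, or FGIS groups". Under Key Outcomes the sample is also counted in patients: "90 patients (30 per group), calculated for 80% power and alpha of 0.05". The effect behind that number is a standardised difference of 0.5 in accuracy, and one patient in ten is expected to be lost.

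**Implants per patient.** The inclusion criteria define partial edentulism as "missing one or more teeth in an arch with remaining natural teeth", with no upper limit. Section 4 of the CBCT imaging protocol provides a medium field of view "for larger edentulous spans or multiple implants".

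**Level of measurement.** Section 6 of the CBCT imaging protocol measures accuracy as each implant's deviation in position, angle and depth from its plan. RFA stability is likewise a reading taken on an implant.

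**Analysis.** The Statistical Analysis list in section 6 gives one comparative method, "Comparative analysis: One-way ANOVA with Tukey post hoc test for group differences", and one subgroup, "Subgroup analysis: Canine vs. molar implants". It does not state what one observation is. The protocol does not limit patients to one implant, name a study implant, average within patient, or mention a model with a patient effect.

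**The concern.** Implants in one mouth share bone, anatomy, operation and planning, so their deviations and stability readings are likely to be positively correlated. The technique is allocated once per patient, so every implant in a patient carries the same allocation. One-way ANOVA assumes independent observations. With one value per patient that assumption is met. With one row per implant it is not: the pooled within-group variance is divided by too large a count, and both the overall F test and the Tukey comparisons, which use that same variance, reject too often.

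Placement accuracy is the outcome used to size the trial, so the ambiguity falls on its main comparison. The canine/molar subgroup sharpens it. Site is a property of the implant, and a patient treated at both sites contributes to both categories. That analysis cannot be run on one value per patient, so the stated method does not fit it whenever a patient has more than one implant.

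**Working it through.** **The plan's own figure.** The stated 90 patients do not follow from the stated inputs. A two-sided comparison of two means at d = 0.5, 80% power and alpha 0.05 needs 2 × (1.96 + 0.84)² / 0.5² ≈ 63 per arm. That is 63 / 0.9 = 70 after 10% dropout, or 210 over three arms. This is a separate matter and neither supports nor weakens the present point. What matters here is that the count is in patients: 30 per arm, or 30 × 0.9 = 27 after dropout.

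**Inputs.** From the protocol: three arms, patients as the randomised unit, 30 per arm (27 after dropout), one-way ANOVA at 5%. Assumed, because the documents give neither: m implants per patient, and a within-patient correlation (ICC) of 0.1, 0.3 or 0.5.

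**Step 1, design effect.** With implants as rows, the true variance of an arm mean exceeds the one ANOVA uses by DE = 1 + (m − 1) × ICC. The standard error used is then 1/√DE of the correct one. For example, m = 2 and ICC 0.3 give DE = 1 + 1 × 0.3 = 1.3, and 1/√1.3 = 0.88.

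**Step 2, type I error by simulation.** One-way ANOVA on implants with no treatment effect, 30 patients per arm, 40,000 trials per setting.

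**Step 3, hand check.** With three groups the F statistic has 2 numerator degrees of freedom. In large samples P(F > c) = exp(−c), so the 5% cut-off is −ln 0.05. Inflating F by DE gives a true error of exp(ln 0.05 / DE) = 0.05^(1/DE). For DE = 1.5 this is exp(−2.996 / 1.5) = 13.6%.

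| m | ICC | DE | SE used / correct SE | Simulated error | 0.05^(1/DE) |
|---|---|---|---|---|---|
| 2 | 0.1 | 1.1 | 0.95 | 6.4% | 6.6% |
| 2 | 0.3 | 1.3 | 0.88 | 10.0% | 10.0% |
| 2 | 0.5 | 1.5 | 0.82 | 13.6% | 13.6% |
| 3 | 0.1 | 1.2 | 0.91 | 8.4% | 8.2% |
| 3 | 0.3 | 1.6 | 0.79 | 15.3% | 15.4% |
| 3 | 0.5 | 2.0 | 0.71 | 22.5% | 22.4% |

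**Step 4, second simulation.** With 27 patients per arm and 6,000 runs, the errors at ICC 0.1 / 0.3 / 0.5 were 6.9 / 9.8 / 13.4% for m = 2 and 9.3 / 14.8 / 22.0% for m = 3. At an average of 1.5 implants per patient they were 5.8 / 8.1 / 10.8%.

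**Step 5, the remedy.** In the 30-per-arm simulation, ANOVA on patient means had an error between 4.8% and 5.1% in all six settings. With m = 1, DE = 1 and there is no inflation.

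**The case against.** The strongest reply is that the protocol never says each implant is a separate row. Groups are described in patients throughout, the analysis is by intention to treat, and one value per patient is a natural reading under which the ANOVA is sound. A statistical analysis plan may exist and could settle the unit. This largely stands. A reader might infer that the plan does analyse implants as independent, and that its standard errors are therefore too small. The text does not support that: the subgroup line shows an implant-level factor in one analysis, not the row structure of the main comparison.

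The size is also conditional. It needs implants as rows, several implants in enough patients, and a positive correlation. At 1.5 implants per patient and ICC 0.1 the error is 5.8%, close to nominal. The 22% end needs three implants per patient and ICC 0.5, and nothing in the documents points to either.

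Three further inferences should not be drawn:
- **Early failure.** It is binary, and these ANOVA figures do not cover it. For categorical variables the analysis section names only frequencies.
- **Subgroup tests.** The protocol does not say that canine and molar sites are tested separately, and a subgroup limited to those sites does not remove other sites from the main analysis.
- **Direction.** Anti-conservatism applies to the technique comparison. For a canine-molar contrast within the same patient, ignoring the pairing can make the standard error too large.

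The reply does not dispose of the point. The protocol has gone beyond leaving detail open: it fixes a method with no patient term alongside a subgroup that is necessarily implant-level. An analysis plan that handled implant-level data correctly would have to depart from the method stated here.

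**Conclusion.** The point holds as an undefined unit of analysis combined with a method that is valid only under one of the two possible units. It concerns accuracy, RFA stability and the canine/molar subgroup. Surgical duration, pain, swelling and satisfaction are patient-level and unaffected.

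If implants are entered as rows, and assuming ICC 0.1 to 0.5, the nominal 5% test of technique runs at about 6-14% with two implants per patient and 8-22% with three, with standard errors 5% to 29% too small. If one value per patient is used, there is no inflation. Confidence is medium, because the protocol does not say which will be done and gives neither the number of implants per patient nor their correlation. It is a cheap improvement, not evidence that the planned analysis is invalid.

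**What to change.** Amend the Statistical Analysis list in section 6 of the protocol:

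1. State that the patient is the unit of analysis for all comparisons between techniques.
2. For accuracy and RFA, give the one-way ANOVA with Tukey one value per patient: either the mean over that patient's implants or a single index implant. Say which. An index implant must be named before randomisation, so that the choice cannot depend on the allocated technique.
3. Analyse implant-level data, including the canine/molar subgroup, with a linear mixed model containing technique, site, their interaction and a random patient intercept. Label it exploratory. The interaction addresses whether the technique effect differs by site, and the random intercept handles patients who contribute to both sites.

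The cost is a few sentences and slightly more analysis work. The number of patients stays at 90. Intervals will be somewhat wider than if implants were counted as independent: under the assumptions above the standard error is larger by a factor of √1.1 = 1.05 to √2.0 = 1.41.

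### One-way ANOVA, the only comparison named, leaves out patients without a 6-month value and cannot use partial follow-up; a mixed model for RFA and censored failure times would serve the intention-to-treat aim better, for a modest gain.

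*Protocol*

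**What the plan says.** Protocol, section 6, Statistical Analysis, fixes one method for comparing the groups: "Comparative analysis: One-way ANOVA with Tukey post hoc test for group differences". The same list closes with "Analysis will follow an intention-to-treat approach". It does not define the intention-to-treat set or say how repeated readings enter the ANOVA.

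Protocol, section 3, Key Outcomes, includes:
- "Implant stability (via Resonance Frequency Analysis at 3, 6, and 12 months"
- "Early implant failure rates (within 6 months"
- patient satisfaction, measured once, at 6 months.

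The sample size statement there gives "90 patients (30 per group), calculated for 80% power and alpha of 0.05", for implant placement accuracy, "with a 10% dropout rate". This is the only loss figure in the document. The CBCT imaging protocol (section 6) takes the accuracy scan within 1 week of surgery.

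Section 5 (Voluntary Participation) allows withdrawal at any time. Section 6 (Blinding) says that surgeons and participants know the technique.

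**The concern.** One-way ANOVA takes one value per patient. Applied to the month-6 RFA readings, it drops a patient who was measured at month 3 and then left, and the 3-month reading goes unused. For early failure, a patient who leaves at month 4 with the implant in place has been followed for four of the six months. ANOVA has no place for that information, so the patient is either left out or assigned an outcome.

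Stability and satisfaction are part of the primary objective (section 2), and early failure is a key outcome. Without further provision, their 6-month comparisons would rest on the patients observed at month 6 but carry an intention-to-treat label. Departures could differ by arm because treatment is open.

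The calendar adds to the risk. Recruitment closes on 3 February 2025 and final follow-up is 3 August 2025, exactly six months later. For the last patients enrolled, any gap between enrolment and surgery moves the 6-month visit past the end of the study, even if they never withdraw.

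**Working it through.** **The plan's own figure.** For a pairwise comparison at d = 0.5, two-sided alpha 0.05 and 80% power, n = 2(1.960 + 0.842)²/0.5² = 62.8, so 63 per arm. Dividing by 0.9 for dropout gives 70 per arm, or 210 in all. The stated 90 is not reproduced. That is a separate matter; only the 10% is carried forward here.

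**Patients analysed.** 10% of 90 = 9, leaving 81, or 27 per arm if losses are even. Applying the 10% at month 6 is an assumption, since it is stated for an outcome measured within a week of surgery.

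**RFA, equal dropout.** Let ρ be the correlation between the 3- and 6-month readings (assumed 0.5 to 0.8; not in the protocol), with SD set to 1. Suppose 27 patients in an arm have both readings and 3 have only the 3-month one.
- Variance of the arm mean at month 6 from observed values only: 1/27 = 0.0370.
- Variance when the 3-month readings are used (large-sample form): (1 − ρ²)/27 + ρ²/30.

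| ρ | Variance using both visits | Reduction |
|---|---|---|
| 0.5 | 0.0361 | 2.5% |
| 0.7 | 0.0352 | 4.9% |
| 0.8 | 0.0347 | 6.4% |

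With the same dropout fraction and mechanism in each arm, the completer means shift equally and the difference between arms is unbiased.

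**RFA, unequal dropout.** Assume that a patient leaves when −(3-month reading) + standard normal noise exceeds its upper p quantile, so low readings drive dropout. With c = Φ⁻¹(1 − p), the mean 3-month reading among completers is shifted by φ(c) / [(1 − p)√2].
- p = 0.05: 0.1031/(0.95 × 1.414) = 0.077 SD.
- p = 0.15: 0.2332/(0.85 × 1.414) = 0.194 SD.
- Difference: 0.117 SD. The month-6 bias is ρ times this.

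| ρ | Bias, 5% vs 15% | Bias, 0% vs 20% |
|---|---|---|
| 0.5 | 0.059 SD | 0.124 SD |
| 0.7 | 0.082 SD | 0.173 SD |
| 0.8 | 0.094 SD | 0.198 SD |

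The standard error of the difference at 5% versus 15% is √(1/28.5 + 1/25.5) = 0.273 SD. The bias in that column is therefore about a fifth to a third of a standard error (0.059/0.273 = 0.22; 0.094/0.273 = 0.34). A model that keeps the 3-month reading removes it when dropout depends only on observed readings.

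**Early failure.** The protocol gives no failure rate, so no size is attached. The point is structural: censoring uses follow-up up to the last implant check, and ANOVA cannot.

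**The case against.** A reader might infer that the protocol contradicts itself, because ANOVA cannot be an intention-to-treat analysis. The document does not support that. Patients can be compared by assigned arm with ANOVA, and ANOVA can be run on imputed data. The protocol does not describe a visit-by-visit or completer analysis and does not rule out imputation. A rule for missing data is commonly left to the SAP, which is not shown, so its absence alone is no finding. What stands is narrower: the one method that is named does not, on its own, use the data that partly followed patients provide.

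A reader might also infer that the plan expects 10% loss at month 6. It does not say so.

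Third, a reader might infer that the scoring of patients who leave would decide the failure comparison. Take 0 versus 3 failures and 3 leavers in each arm, purely as an illustration:
- leavers counted as successes, 0/30 vs 3/30: Fisher p = 0.24
- leavers omitted, 0/27 vs 3/27: p = 0.24
- leavers counted as failures in both arms, 3/30 vs 6/30: p = 0.47.

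No rule applied alike to both arms crosses 0.05.

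The proposed methods also have limits. A mixed model still omits anyone with no reading, and for satisfaction, measured once, only the label changes. That ANOVA does not suit a binary failure outcome is true whatever the dropout.

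**Conclusion.** The concern holds as an improvable choice of method, not as a contradiction. Under the assumptions above, the cost for RFA is a 2.5 to 6.4% larger 6-month variance if dropout is equal, and less than 0.10 SD of bias, against a standard error of 0.27 SD, if it splits 5% versus 15%. The more extreme split of 0% versus 20% would give 0.12 to 0.20 SD. The dropout level at month 6, its split between arms, its dependence on the 3-month reading and the correlation are all assumed. For early failure the loss of partial follow-up is real but cannot be sized from the document. The change is worth making because it is cheap, not because the effect is large.

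**What to change.** In section 6, Statistical Analysis:

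1. **RFA.** Replace the ANOVA with a mixed model for repeated measures on the 3- and 6-month readings, by assigned technique, with terms for technique, visit and technique-by-visit and Tukey-adjusted pairwise contrasts. State how a failed implant is handled: it gives no RFA value, and that absence depends on the outcome, so the model does not deal with it by itself. The 12-month reading is left out here because it falls after the stated final follow-up date.
2. **Early failure.** Replace the ANOVA with Kaplan-Meier estimates to 6 months from placement, censoring at the last implant check, and name a log-rank or exact test between groups. Add a best-case/worst-case bound for patients without a 6-month status, using the same rule in all arms.
3. **Satisfaction.** Describe the result as applying to patients assessed at month 6.

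No new patient, visit or measurement is needed. The cost is slightly more programming and reliance on a missing-at-random assumption for RFA, with the matching assumption of non-informative censoring for failure.
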